Coenzyme Q10 (CoQ10) is a fat-soluble antioxidant occurring naturally in the inner membrane of the cell's mitochondria. It plays an essential role as a diffusible electron carrier in the electron transport chain (18, 19). CoQ10 has two forms: the oxidized form and the reduced, active form. This reduced form is widely used in the adjunctive treatment of cardiovascular diseases, nutritional health products, and food additives (20). Notably, CoQ10 plays a key role in myocardial hypoxia, significantly boosting heart health. In patients with myocardial ischemia and hypoxia, ubiquinol, the reduced-form supplement (19, 21, 22), increases aerobic metabolism efficiency and raises the anaerobic threshold. This signifies a lesser need to resort to anaerobic energy production at the same workload (19, 21, 22). Ubiquinol is necessary for the body to produce energy; however, its content in the organism decreases with age and may lead to diseases (23). The lack of ubiquinol causes less efficiency, quick fatigue, and weakened cellular protection ability against oxidative stress (19). These clinical trials implied that ubiquinol could reverse the loss of physical performance ability both at high altitudes and at return to sea level.

We designed this double-blinded, placebo-controlled clinical trial to investigate the hypothesis that ubiquinol supplementation could improve cardiorespiratory fitness, which may be impaired during high-altitude acclimatization and de-acclimatization. This novel Shigatse CARdiorespiratory Fitness (SCARF) study has the potential to identify whether ubiquinol supplementation may rescue the loss of exercise capacity and impaired cardiorespiratory fitness during acute hypoxia and the reoxygenation process. We believe this is the first study that prospectively and accurately evaluates cardiorespiratory fitness during high-altitude acclimatization and de-acclimatization. We also explore the effect of ubiquinol on blood metabolic substrate and automatic nervous function to illustrate the possible beneficial mechanisms further.

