Cardiac output (CO)	Measures the strength of cardiac ejection	Using the equilibrium CO_2_ re-breathing technique of Collier (36).
Exercise ventilatory power (EVP)	An integrated index to predict risk representing synergistically linked assessment of ventilatory efficiency and hemodynamics, peak SBP reflecting systemic hemodynamics (37), and VE/VCO_2_ slope reflecting the complex interplay of peripheral and pulmonary abnormalities.	The ratio between peak SBP and the VE/VCO_2_ slope (38).
Circulatory Power (CP)	An index of cardiac systolic function (39).	The product of CO and mean arterial BP (40).
Dead space volume/tidal volume (VD/VT)	An estimate of the ventilation-perfusion ratio representing the efficiency of alveolar ventilation and blood flow matching. The physiological dead space is normally one-third of the tidal volume at rest (36).	[(PaCO_2_ − PECO_2_)/PaCO_2_] − (VDapp/tidal volume) where PaCO_2_ is the arterial CO_2_ pressure, PECO_2_ is the partial pressure of CO_2_ in mixed expired air, and VDapp is the apparatus dead space. PaCO_2_ can be estimated noninvasively using PETCO_2_ (41).

The secondary outcomes will be the questionnaire results of AMS and HADAS. The symptoms of these two diseases are shown in a later section. The effects of altitude and ubiquinol on them will be analyzed in detail in this study. Participants with severe disease symptoms, especially hypoxia-related symptoms, will receive additional treatment.

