### Study design

2.6.

Figure 1 shows the flow chart of this study. Participants will take ubiquinol orally with a dose of 200 mg daily or a placebo for 14 days before departure. Physical examination, symptoms related to high-altitude acclimatization and de-acclimatization, cardiorespiratory exercise test, laboratory test, and any possible adverse reaction of ubiquinol and exercise will be collected at baseline detection and each visit. During the 14 days of the medication, only participants who did not experience these adverse effects would go to the high altitude as scheduled. It would help us identify related symptoms at high altitudes due to hypoxia rather than adverse events of ubiquinol. The laboratory and exercise tests will be conducted separately on the last three days of the 14 days. Subsequently, they will board a flight to Shigatse (high altitude area, 3,900 m) in 3 h. After arriving at Shigatse, the AMS symptom self-administered questionnaires and adverse reactions of ubiquinol will be followed up daily, and the other prior programs will be carried out on the third day. The subjects will then be flown back to a low altitude after staying for 7 days at a high altitude and scored for HADAS, followed by other prior programs at a low altitude on the 7th day after return. The last visit will be set in the sixth month of this study, which has not yet been conducted. Laboratory tests include a blood routine test of 19 parameters commonly used in the clinic and a serological test of 19 circulating indicators, including glucose, total cholesterol, triglyceride, low-density lipoprotein cholesterol, high-density lipoprotein cholesterol, lactate, non-esterified fatty acid, norepinephrine, epinephrine, plasma renin activity, angiotensin Ⅱ, angiotensin-converting enzyme 2, neuropeptide Y, atrial natriuretic peptide, lactate dehydrogenase, insulin, glucocorticoid, adiponectin, and leptin.

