### Laboratory tests

2.7.

Participants will be requested to avoid eating or drinking anything apart from water for up to 12 h. Participants' blood samples will be collected between 8:00 and 8:15 am the day before the exercise tests at different altitudes using the same procedure. After sitting quietly for 15 min, approximately 5 ml of intravenous blood of participants will be collected from the vein at the cubital fossa in the elbow with a tourniquet and mixed immediately with 1 ml of the anticoagulant, dipotassium ethylenediaminetetraacetic acid. Blood samples will be divided into 1 ml and 4 ml parts. The first 1 ml will be analyzed using a BC-3000 plus automated hematology corpuscle analyzer (Shenzhen, China), and the 4 ml will be subjected to high sensitivity enzyme-linked immunosorbent assay kit (Jiangsu Jingmei Biological Technology Co., Ltd., China) for the 19 kinds of circulating parameters. Blood collected at high altitude will be frozen in a −20°C transfer tank and flown to Xinqiao Hospital within 3 h. All blood samples will be measured for biochemical parameters at the Clinical Laboratory of Cardiology Science of Xinqiao Hospital.

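### Section 2.7 assigns one ELISA kit line to all 19 circulating markers, although an antibody-binding assay is not a suitable method for seven of them (glucose, lactate, non-esterified fatty acid and four lipid measures)

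*Protocol article*

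**What the plan says.** Section 2.6 of the protocol article describes "a serological test of 19 circulating indicators, including glucose, total cholesterol, triglyceride, low-density lipoprotein cholesterol, high-density lipoprotein cholesterol, lactate, non-esterified fatty acid". The list continues through catecholamines ("norepinephrine, epinephrine, plasma renin activity" stand together there), vasoactive peptides, lactate dehydrogenase and metabolic hormones.

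Section 2.7 divides each blood sample in two. The 1 ml part goes to a haematology analyser. For the larger part, "the 4 ml will be subjected to high sensitivity enzyme-linked immunosorbent assay kit", with one manufacturer given, "for the 19 kinds of circulating parameters". The section ends: "All blood samples will be measured for biochemical parameters at the Clinical Laboratory of Cardiology Science of Xinqiao Hospital". That sentence gives the place of measurement and no second method.

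The Introduction gives the purpose of the markers: "We also explore the effect of ubiquinol on blood metabolic substrate and automatic nervous function". The Discussion returns to this twice, planning to relate circulating substances to exercise performance and to look for a mechanism through markers of metabolism. Section 2.5 does not list the markers as primary or secondary outcomes. The primary outcome is the set of exercise-test variables, and "The secondary outcomes will be the questionnaire results of AMS and HADAS".

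**The concern.** An ELISA detects an antigen through antibody binding. That suits hormones, peptides and other proteins. Glucose, lactate, fatty acids and triglyceride are small molecules or lipids, ordinarily quantified by enzymatic chemistry. LDL and HDL cholesterol are defined by the cholesterol content of a lipoprotein fraction, which antibody binding to a particle does not give. If section 2.7 is followed literally, the value recorded under each of these names may not be the named quantity and may not be comparable with ordinary clinical values.

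What is at stake is the mechanistic part of the trial. The stated interest in metabolic substrates rests on these analytes, and the planned correlations with exercise capacity would use them. Section 2.4.1 also counts abnormal blood results among the safety endpoints. It does not say whether the 19 markers are included. If they are, judging abnormality needs values that can be set against clinical reference ranges.

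This is not simply detail left out of a condensed article. The text fixes a method, with kit type, manufacturer, aliquot and anticoagulant.

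**Working it through.** No sample-size or error-rate formula is involved. The check is a count, followed by a comparison of method with analyte.

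**Step 1: scope of the ELISA sentence.** Counting the names in section 2.6:

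- Metabolites and lipids: glucose, total cholesterol, triglyceride, LDL cholesterol, HDL cholesterol, lactate, non-esterified fatty acid = 7.
- Enzyme-related: plasma renin activity, lactate dehydrogenase = 2.
- Catecholamines, peptides, proteins and a steroid: norepinephrine, epinephrine, angiotensin II, angiotensin-converting enzyme 2, neuropeptide Y, atrial natriuretic peptide, insulin, glucocorticoid, adiponectin, leptin = 10.

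7 + 2 + 10 = 19. This reproduces the figure of 19 in both sections, so no listed marker falls outside the ELISA sentence.

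**Step 2: is another method named?** The only other instrument in section 2.7 is the haematology analyser, which is used for the 1 ml part. No enzymatic, colorimetric or activity assay appears anywhere in the article.

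**Step 3: does the method fit each group?** This step rests on general assay knowledge, because the article gives no kit principle, working range, units or validation.

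- For the 10, an immunoassay is plausible.
- For the 2, it depends on what the kit reads. Renin activity can be obtained by immunoassay of the angiotensin I generated in a timed step, so ELISA is not wrong in itself; the text does not describe such a step. Lactate dehydrogenase is listed without saying activity or concentration.
- For the 7, antibody binding is not a suitable principle.

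**Step 4: size.** Clearly mismatched: 7/19 = 37%. Needing a definition: 2/19 = 11%. Table 1 schedules serum markers at three visits (days 11, 17 and 28). With the planned 41 participants, the mismatched analytes account for at most 7 × 3 × 41 = 861 of 19 × 3 × 41 = 2,337 marker values.

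**Step 5: which conclusions depend on them?** The primary outcome comes from the exercise-testing system, and the secondary outcomes come from symptom scores. Neither uses the 19 markers.

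**The case against.** The strongest reply is that the article does not show a wrong assay, only doubtful wording. It names a supplier, gives no assay principle, and says that biochemical parameters are measured in the hospital's clinical laboratory. The ELISA phrase may be shorthand for a mixed set of kits. This stands, and it limits the conclusion: a reader might infer that the seven results will certainly not be the named quantities, but the documents do not go that far. It does not remove the need for correction. If the wording is loose, section 2.7 misstates the method; if it is literal, the method does not suit seven analytes.

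Other stronger readings are tempting and are not supported:

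- **Nine faulty markers (9/19 = 47%).** This would add renin activity and lactate dehydrogenase. The first can validly be read by immunoassay, and the second is not described as an activity. Both need a definition; neither is shown to be mismatched.
- **Values too concentrated for the kits.** An argument from millimolar concentrations and heavy dilution needs a kit range, which the article does not give. Dilution is also routine in immunoassay and does not by itself invalidate a result.
- **Spurious treatment effects.** Allocation is randomised, laboratory staff are blinded (section 2.4.1), and blood is collected by the same procedure at each altitude (section 2.7). Assay error unrelated to arm mainly adds noise and reduces sensitivity. Nothing in the documents supplies a mechanism for a false difference between arms.

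It is also fair to say that the markers are exploratory and that the main conclusions of the trial do not rest on them.

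**Conclusion.** The point holds in a limited form. As written, one ELISA kit line is assigned to all 19 circulating markers, and for seven of them (37%) that is not a suitable method. The results for glucose, lactate, non-esterified fatty acid and the four lipid measures are therefore not assured to be the quantities named, and they include all the metabolic substrates on the list. Two further markers, renin and lactate dehydrogenase, need the measured quantity defined.

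The conclusion assumes that the ELISA sentence means what it says, and it relies on general knowledge of assay principles rather than on anything the article states about the kits. No size of measurement error can be derived from the documents. The consequence is confined to the exploratory mechanistic findings, and to the safety review only if the 19 markers belong to it. The primary and secondary outcomes, the sample size and the error rate are unaffected.

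**What to change.** In section 2.7:

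- Assign glucose, total cholesterol, triglyceride, LDL cholesterol, HDL cholesterol, lactate and non-esterified fatty acid to enzymatic chemistry assays. If other assays were in fact used, correct the text to name them.
- Keep ELISA for the hormones and peptides.
- State whether renin and lactate dehydrogenase are measured as activity or concentration, and name them accordingly in section 2.6.

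If the wording was loose, the cost is a text correction. If it was literal, the cost is a change of platform for seven routine analytes, and its feasibility is uncertain. Enrolment ended in June 2022, only the six-month visit is described as outstanding, and Table 1 schedules no blood tests then, so collection appears complete. Whether assays have been run or volume remains is not stated. The samples are in EDTA, those from high altitude are frozen at −20°C, and no plasma separation is described, so their suitability for each enzymatic assay must be checked first.

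If the samples are already assayed or prove unsuitable, report the seven with the assay principle actually used and limit the mechanistic conclusions drawn from them.

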#### Statistical considerations

2.11.2.

Continuous variables will be expressed as means ± standard deviations (SD) or as median (interquartile spacing), and categorical variables as *n* (%) according to the Shapiro–Wilk test. Generalized estimating equations (GEE) with an exchangeable working correlation will be employed. Treatment, altitude, and the treatment multiplied by altitude interaction will be considered independent variables under mixed models. At each altitude, a comparative analysis will be carried out between two groups (ubiquinol group and placebo group), and the least significant difference method will be performed to adjust within-altitude differences for multiple comparisons. Correlation analyses will be performed using Pearson correlation for continuous variables, and Spearman Rank tests will be used between categorical variables. In addition, subgroups will be defined by age for analysis since it is known that ubiquinol levels decrease with age (23). Two-sided tests with *p*-values less than 0.05 will be considered statistically significant. IBM SPSS Statistics software for Windows (version 26, IBM, Armonk, NY, United States) will be used for statistical analyses.

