Cardiorespiratory fitness reflects the comprehensive ability of the body to transport and utilize oxygen and embodies the overall function of the respiratory and cardiovascular systems (49, 50). VO_2_max is the gold standard for assessing cardiorespiratory fitness and an independent predictor of cardiovascular events and mortality (51–53). Previous studies have indicated that VO_2_max decreases linearly by approximately 8% for every 1,000 m of additional elevation above 700 m, while it descends in an accelerated curve over 6,300 m, suggesting that cardiorespiratory function is impaired at high altitudes (54). However, there is limited information on cardiorespiratory fitness changes during de-acclimatization from a high altitude in healthy individuals, and the underlying mechanisms remain to be elucidated. Thus, in this study, we try to illuminate the possible mechanism by circulating markers of metabolism and the autonomic nervous system (55).

This study has some limitations. First, although this is not a small clinical trial in the CPET trial at a high altitude, this study is limited by a small sample size (*n* = 41) and short follow-up (on days 17 and 28, respectively). Therefore, it is troublesome to implement hierarchical analysis, and these preliminary results need to be confirmed in a large cohort. Second, long-term follow-up may be more meaningful in evaluating ubiquinol supplements on cardiorespiratory fitness.

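### The low-versus-high altitude comparison of circulating markers describes no adjustment for haemoconcentration, so plasma-confined markers could show an altitude change without any change in circulating amount (minor, exploratory measures).

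*Protocol article*

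**What the plan says.** Study design lists "a serological test of 19 circulating indicators, including glucose, total cholesterol, triglyceride" and others: lipids, lactate, catecholamines, plasma renin activity, lactate dehydrogenase, adiponectin and further hormones. It also lists "a blood routine test of 19 parameters commonly used in the clinic", whose items are not named. Table 1 schedules both on days 11, 17 and 28. At altitude, "the other prior programs will be carried out on the third day".

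Under Laboratory tests, about 5 ml of venous blood is "mixed immediately with 1 ml of the anticoagulant, dipotassium ethylenediaminetetraacetic acid" and then divided. "The first 1 ml will be analyzed using a BC-3000 plus automated hematology corpuscle analyzer", while "the 4 ml will be subjected to high sensitivity enzyme-linked immunosorbent assay kit". So the blood count and the markers come from one draw. The text describes no separation of plasma.

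Statistical considerations gives the model: "Treatment, altitude, and the treatment multiplied by altitude interaction will be considered independent variables under mixed models". The arms are also compared within each altitude. Nothing there mentions haemoglobin, haematocrit or plasma volume.

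The Discussion states the purpose of the markers: "we try to illuminate the possible mechanism by circulating markers of metabolism and the autonomic nervous system".

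**The concern.** A concentration is an amount divided by a volume. The altitude term attributes each within-person change in concentration to altitude, and the Discussion wants to read such changes as metabolic or autonomic mechanism. If plasma volume shrinks in the first days at 3,900 m, a marker that stays in plasma becomes more concentrated although its amount is the same. If plasma volume then recovers after descent, the marker falls back. Up at day 17 and down at day 28 is the shape expected of acclimatization followed by de-acclimatization, and several plasma-confined markers would follow it together.

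Randomisation does not remove this from the altitude effect, because every participant makes the same journey. Any correlation between markers and performance that pools altitudes would be exposed as well. At stake is the mechanistic account of altitude for some of the markers. The estimate of what ubiquinol does is not at stake.

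**Working it through.** The article gives no figure on haemoconcentration, so there is no figure of the plan's own to reproduce. The calculation below is illustrative.

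**Inputs from the article.** Three blood visits (days 11, 17, 28); sample size 39 before dropout; two-sided 0.05; correlation among repeated measures 0.5 (set in Sample size for the trial, and borrowed here for the markers).

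**Assumed inputs.** Baseline haematocrit 0.43; haemoglobin rise of 3, 5 or 8% with a proportional haematocrit rise; constant red-cell mass; marker CV of 15, 20, 30 or 50%.

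**Step 1: plasma volume.** The haemoglobin–haematocrit formula is PV2/PV1 = (Hb1/Hb2) × (1 − Hct2)/(1 − Hct1). For a 5% rise, Hct2 = 0.43 × 1.05 = 0.4515, so PV2/PV1 = (1/1.05) × (0.5485/0.57) = 0.9165, a fall of 8.4%.

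**Step 2: apparent rise in a plasma-confined marker.** This is 1/(PV2/PV1) − 1. For the same case, 1/0.9165 − 1 = 9.1%.

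**Step 3: chance of p < 0.05 with no true change.** The test is a paired t test with n = 39. The SD of the within-person change is CV × √(2 × (1 − 0.5)) = CV. The noncentrality is rise/CV × √39; at 9.1% and CV 20% it is 0.0912/0.20 × 6.245 = 2.85, giving 79%.

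| Hb rise (assumed) | Plasma volume | Apparent rise | CV 15% | CV 20% | CV 30% | CV 50% |
|---|---|---|---|---|---|---|
| 3% | −5.1% | +5.4% | 59% | 37% | 19% | 10% |
| 5% | −8.4% | +9.1% | 96% | 79% | 46% | 20% |
| 8% | −13.0% | +14.9% | >99% | >99% | 86% | 44% |

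The nominal rate is 5%.

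**Step 4: dependence on the material assayed.**
- Liquid anticoagulant: 1 ml added to 5 ml of blood leaves a plasma fraction of 5(1 − Hct)/(5(1 − Hct) + 1). In the 5% case the rise becomes 8.0% instead of 9.1%.
- Whole blood: a plasma-confined marker rises by 1.0912 × 0.5485/0.57 − 1 = 5.0%. Applying the plasma-volume factor to that value would overcorrect: 1.05 × 0.9165 − 1 = −3.8%.

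**Step 5: the randomised comparison.** If both arms lose the same fraction of plasma, both arm means at that altitude are multiplied by the same factor and the ubiquinol/placebo ratio is unchanged.

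**The case against.** The strongest objection is that this rests on silence. The article is condensed, the full protocol and analysis plan are not shown, and nothing says that concentrations will go uncorrected. That stands as a limit: what can be said is that no adjustment is described. It does not dispose of the point, because the article does state the model terms and the mechanistic use of the markers, and together these assign a concentration change to altitude.

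A second objection is that the size comes from outside the article. This also stands. The haemoglobin rise, the baseline haematocrit, the CVs, recovery by day 28 and the presence of haemoglobin and haematocrit in the blood count are all assumptions. At the small end of the range the false-signal chance is only about 10 to 59%.

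A reader might infer that all 19 markers are pushed up together and will be misread. The documents do not support that. The list includes glucose, lactate, insulin and catecholamines, which are regulated, diffusible or quickly cleared, and plasma renin activity, which is a rate; none of these need scale with plasma volume. For the same reason, a rule accepting an altitude change in any marker only if it survives correction would be unsound. With haemoglobin up 5%, correction would turn a truly unchanged regulated concentration into an 8.4% fall and would erase a genuine 9% rise.

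Finally, the markers are neither the primary outcome (exercise-test measures) nor the secondary outcomes (mountain sickness and de-acclimatization symptoms). That is correct and sets the weight of the point.

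**Conclusion.** The point holds in a limited form. As described, the altitude comparison of marker concentrations has no safeguard against haemoconcentration, although a blood count is taken from the same draw. For markers largely confined to plasma, such as lipoprotein lipids, lactate dehydrogenase and adiponectin, an assumed haemoglobin rise of 3 to 8% would produce an apparent rise of about 5 to 15% at day 17 (about 3 to 8% if whole blood is assayed). It would reverse by day 28 only if plasma volume recovers. This may be mistaken for an acclimatization and de-acclimatization effect.

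The randomised, primary and secondary comparisons are essentially unaffected. This is a minor point on exploratory laboratory measures. It would lapse if the full plan already contains such a correction.

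**What to change.** - For the altitude contrasts (day 11 to 17 and day 11 to 28), report plasma-volume-corrected marker values beside the measured ones as a sensitivity analysis. Use each participant's haemoglobin and haematocrit from the same draw, after confirming that both are among the 19 blood-count parameters.
- State whether plasma or whole blood is assayed, and match the correction to it.
- Classify the markers before unblinding. For plasma-confined markers, interpret an altitude change as mechanistic only if it also appears after correction. For regulated, diffusible or rapidly cleared markers, show both values without a pass/fail rule.
- Leave same-altitude comparisons of ubiquinol and placebo uncorrected.

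The cost is one derived variable, with no new sample or visit. The correction assumes near-constant red-cell mass over these weeks, which should be stated with the results.
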